**Methods:**

Multi-centre cohort study using participatory action research guided by the Knowledge-to-Action Framework. ACCHS supportive of enhancing services for chronic lung disease will be recruited. Aboriginal Health Workers (AHW) and the exercise physiologist (EP) or physiotherapist (PT) within these ACCHS will attend a workshop aimed at increasing knowledge and skills related to management of COPD and the provision of PR. Indigenous people with COPD will be invited to attend an 8-week, twice weekly, supervised PR program. Outcomes: AHW, EP/PT knowledge, skills and confidence in the assessment and management of COPD will be measured before and immediately after the *BE WELL* workshop and at 3, 6 and 12 months using a survey. PR participant measures will be exercise capacity (6-minute walk test (6MWT), health-related quality of life and health status at commencement and completion of an 8-week PR program. Secondary outcomes will include: number, length and cost of hospitalisations for a COPD exacerbation in 12-months prior and 12-months post PR; local contextual factors influencing implementation of PR; specific respiratory services provided by ACCHS to manage COPD prior to project commencement and at project completion. Repeated measures ANOVA will be used to evaluate changes in knowledge and confidence over time of AHWs and EP/PTs. Paired t-tests will be used to evaluate change in patient outcomes from pre- to post-PR. Number of hospital admissions in the 12 months before and after the PR will be compared using unpaired t-tests.

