## Methods/design

The study will be a cohort study using implementation science and participatory action research methods guided by the Knowledge-to-Action Framework [13–15]. This will be an iterative process of reflection and action carried out with and by ACCHS rather than ‘on’ them [15]. Fig. 1 maps the knowledge already established for PR and the elements of the *BE WELL* program in the Knowledge-to-Action Framework. The study has ethics approval from the Aboriginal Health and Medical Research Council of New South Wales, Australia (Project 1261/17). All participants will provide written, informed consent. Any protocol amendments will be approved by the ethics committee and reported on the Australian New Zealand Clinical Trials Registry.

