	CAT (26)	To evaluate the impact that COPD on wellbeing and daily life	An 8-item questionnaire evaluating symptoms, activity limitations, sleep, confidence		
	Hospitalisations	To evaluate the impact of the *BE WELL* PR program on hospitalisations	Hospital separation data will be collected from the NSW Centre for Health Record Linkage (CHeReL). Administrative hospital records including information on the Diagnostic Related Group (DRG) classification and International Classification of Disease (ICD-10) codes for hospital separations will be used to estimate a cost using local cost weights	Indigenous patients who participated in the *BE WELL* PR program	In the periods 12 months preceding and following participation in the *BE WELL* PR program
	Other healthcare costs (GP visits, medications)	To evaluate the impact of the *BE WELL* PR program on other healthcare costs	Costs of medical services and medications will be recorded from patients who consent to access of their administrative health care use data through the Medical and Pharmaceutical Benefits Schedules (PBS) from Medicare Australia. Additional primary health care and medication use data will be abstracted from primary health care histories particularly in sites where the PBS have limited implementation, e.g. very remote Australian health care services		
	Costs of *BE WELL* pulmonary rehabilitation program	To determine the costs of provision of the *BE WELL* PR program for comparison with any costs savings	Costs of program delivery will include staff time, facility costs, training resources	Executive staff of the ACCHS	During the *BE WELL* project

*ACCHS* Aboriginal community controlled health services, *AHW* Aboriginal health worker, *BE WELL* Breathe easy walk easy lungs for life, *CAT* COPD assessment test, *COPD* Chronic obstructive pulmonary disease, *EP/PT* Exercise physiologist/physiotherapist, *EQ5D-5L* EuroQual 5 dimensions-5 levels, *GP* General practitioner, *HRQoL* Health-related quality of life, *PR* Pulmonary rehabilitation, *SGRQ* St George’s respiratory questionnaire, *6MWT* Six-minute walk test

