## Data and data analysis

Plans for data entry, coding, security, and storage will be held on the secure Research Management Dashboard of the University of Sydney. Quantitative data will be collated and analysed using SPSS statistics package. Scores from the *BE WELL Health Provider Impact Questionnaire* before and immediately after the workshop will be compared using paired t-tests. Repeated measure ANOVA will be used to evaluate knowledge retention over time. For categorical measures of self-rated knowledge, confidence and skills, change scores will be calculated and analysed using Wilcoxon’s signed ranks test. Patient outcomes for exercise capacity and health-related quality of life will be compared before and after PR using paired t-tests. The number of hospital admissions for respiratory related care in the 12 months before and after the *BE WELL* PR program will be compared using unpaired t-tests and the number of patients admitted before and after program will compared using proportions. The costs of delivery of the *BE WELL* program will be determined and potential savings against reductions in health care utilisation will be quantified [30]. For qualitative data, the focus groups with ACCHS staff and with participants in the *BE WELL* PR program and interviews with AHW who participate in the online education sessions will be digitally recorded and transcribed. Data will be analysed in QSR International NVivo using inductive coding and thematic analysis [31]. Any adverse events will be reported immediately to the ethics committee and will be reported in any publications.

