## Sample size

Sample sizes have been calculated for the quantitative measurements. For evaluating changes in health worker knowledge of COPD management, the scores from the objective knowledge test in *BE WELL Health Provider Impact Questionnaire* will be used. The sample size, based on pilot data demonstrating change in knowledge score of 7 marks [standard deviation (SD) 4.5] [32], requires eight AHW participants, with a power of 80%, alpha 0.05, allowing for a 20% dropout (i.e. two AHWs per ACCHS). For the patient outcomes, based on our pilot study in rural and remote areas, to detect a change in 6MWT of 48 m, SD 70 m [11], with a power of 80% and alpha 0.05, 40 patients will be required, allowing for a 15% dropout. For quality of life, to detect a minus 4-point improvement in SGRQ (which is the minimal important difference [33]) with SD 6 points, 42 patients will be required, allowing for a 15% dropout, with power 80% and alpha 0.05. For hospitalisations, we have conservatively assumed a 20% reduction in hospital admissions. Therefore 97 patients would be needed, power 80%, alpha 0.05, allowing for 15% drop-out. Based on the largest patient sample size required, 97 patients with COPD will be recruited. For qualitative data, focus groups and interviews will be undertaken with participants until no new information is obtained and saturation is achieved.

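### Before-and-after hospital admissions from the same patients are to be compared with unpaired t-tests, which discards the pairing at a cost that depends on an unstated within-patient correlation

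*Protocol article*

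**What the plan says.** The test is named twice. In the abstract's Methods: "Number of hospital admissions in the 12 months before and after the PR will be compared using unpaired t-tests". In Data and data analysis, the article says that these admissions "will be compared using unpaired t-tests and the number of patients admitted before and after program will compared using proportions".

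Both counts come from the same people. The Hospitalisations row of Table 1 gives the participants as "Indigenous patients who participated in the" PR program, and the timing as "In the periods 12 months preceding and following participation in the" program. Under Methods/design, "The study will be a cohort study using implementation science and participatory action research methods"; no section defines a control or comparison group.

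The other before-and-after patient outcomes are treated differently: "Patient outcomes for exercise capacity and health-related quality of life will be compared before and after PR using paired t-tests".

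On size, the Sample size section says "For hospitalisations, we have conservatively assumed a 20% reduction in hospital admissions" and "Therefore 97 patients would be needed, power 80%, alpha 0.05, allowing for 15% drop-out". It then recruits to the largest of its calculated patient numbers, which is this one. The abstract lists hospitalisation among the secondary outcomes.

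**The concern.** An unpaired t-test treats the two years as two independent groups of people. Here each patient is his or her own comparison. If patients with many admissions before PR also tend to have more afterwards, the before and after counts are positively correlated. Differences between patients then cancel out of the true variance of the mean change, but they remain in the error term of the unpaired test. The standard error is too large, the confidence interval too wide and the p-value too big.

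The article gives no reason for handling admissions differently from the 6-minute walk test (6MWT) and quality of life, which have the same before-and-after structure and are paired in the same paragraph.

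At stake is efficient use of the data on the outcome that raises recruitment to 97; the next largest requirement is 42, for the St George's Respiratory Questionnaire. Admissions also feed the comparison of program costs with savings from reduced health care use.

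**Working it through.** **The plan's own figure.** The 97 cannot be derived from the stated inputs, because no baseline rate, SD or within-patient correlation is given. It can be matched under an assumption: two independent proportions of 40% and 20%, two-sided alpha 0.05, 80% power.

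n = [1.96 × sqrt(2 × 0.3 × 0.7) + 0.8416 × sqrt(0.4 × 0.6 + 0.2 × 0.8)]² / 0.2² = 1.8025² / 0.04 = 81.2, rounded up to 82. Then 82 / 0.85 = 96.5, rounded up to 97.

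This is a match, not proof of what was done. It gives 82 completers, which is used below.

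**Standard error.** Let the before and after counts have SDs s1 and s2 and correlation rho, in n patients.

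- Variance assumed by the unpaired test: (s1² + s2²)/n.
- True variance of the mean change: (s1² + s2² - 2 × rho × s1 × s2)/n.
- With s1 = s2, unpaired SE / true SE = 1/sqrt(1 - rho).

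**Size and power** (normal approximation, two-sided 0.05). The unpaired test rejects when the change exceeds 1.96/sqrt(1 - rho) true standard errors.

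- Actual type I error = 2 × [1 - Φ(1.96/sqrt(1 - rho))].
- A paired test has 80% power when the true change is 1.96 + 0.8416 = 2.80 true standard errors. The unpaired power for that change is Φ(2.80 - 1.96/sqrt(1 - rho)).

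| rho (assumed) | SE ratio | Actual type I error | Unpaired power when paired is 80% |
|---|---|---|---|
| 0 | 1.00 | 0.050 | 80% |
| 0.1 | 1.05 | 0.039 | 77% |
| 0.3 | 1.20 | 0.019 | 68% |
| 0.5 | 1.41 | 0.006 | 51% |
| 0.7 | 1.83 | 0.0003 | 22% |

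For example, at rho 0.5: 1.96/0.7071 = 2.77, and Φ(2.80 - 2.77) = Φ(0.03) = 51%. A negative correlation would reverse the direction: at rho -0.1 the type I error is 0.062.

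**The same comparison on another scale.** Suppose instead that 82 completers give 80% power under independence, with the effect and SD then held fixed. Unpaired power is Φ(0.8416/sqrt(1 - rho)) and paired power is Φ(2.80/sqrt(1 - rho) - 1.96). At rho 0.1, 0.3 and 0.5 this gives 81% v 84%, 84% v 92% and 88% v 98%. Pairing is better at every positive rho.

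**Check on simulated counts.** Poisson counts with a shared gamma patient effect, 82 patients, mean 1 admission per patient in the year before, 20,000 runs. The mean, the heterogeneity and the reading of the reduction as relative are all assumptions.

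| rho, approx. | 20% fall: unpaired v paired power | 40% fall: unpaired v paired power |
|---|---|---|
| 0 | 27% v 27% | 81% v 81% |
| 0.3 | 15% v 27% | 70% v 81% |
| 0.45 | 8% v 26% | 58% v 80% |
| 0.6 | 3% v 25% | 37% v 78% |

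With a 20% fall and rho about 0.2, the figures are 20% v 26%. At mean 2 and rho about 0.63 they are 9% v 46%.

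**The case against.** **It is a condensed article and the outcome is secondary.** Condensation does not help: the test is not left out but named, in two places, and it is the wrong one for the design. The secondary status does stand. The Outcome measures section rests effectiveness mainly on exercise capacity and quality of life, which are paired, and with positive correlation the unpaired test errs towards caution. This limits how serious the point is.

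**The correlation is unknown, so the loss may be trivial.** This stands in part. At rho 0.1 only about 3 points of power are lost from 80%. A reader might infer that power is always much lower; the document supports no particular rho, so only a range can be given.

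**If 97 was calculated for independent groups, the unpaired test still delivers what was planned.** On that scale its power does stay at or above 80% for positive rho. Even so, it gives up precision that the data already contain.

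**Readings that go too far.**

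- A reader might infer that the unpaired test is why a real reduction would be reported as no change. In the simulations above, the paired test also misses a 20% relative fall in most runs (power about 26% at mean 1 and 46% at mean 2). Under those assumptions the larger problem is the basis of the sample size.
- A reader might infer that the comparison of patients admitted is also wrong. The article names no test for it, and McNemar's test also compares proportions.
- A reader might treat the lack of a count model or an offset for time at risk as an error. These are refinements. Table 1 fixes both windows at 12 months, and in simulation a clustered rate model added only about 3 points of power to the paired t-test (26.6% to 29.3% at mean 1; 46.0% to 49.2% at mean 2).

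**Conclusion.** The point holds. The abstract and the analysis section both specify an independent-samples test for counts taken twice from the same patients, with no justification and against the article's own practice for its other patient outcomes.

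The size depends on the within-patient correlation, which is not given. For rho from 0.1 to 0.7 the standard error is 5% to 83% too large, and a power of 80% for a paired test falls to between 77% and 22%. With no correlation there is no loss. These figures assume equal variances, a normal approximation and a two-sided 0.05 level.

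With positive rho the error is conservative, so it does not produce false claims of benefit. It merits correction because it concerns the outcome that sets recruitment at 97 and because the correction is nearly free.

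**What to change.** In the abstract's Methods and in Data and data analysis, replace the unpaired t-test for admissions with a within-patient comparison. A paired test is the minimum. Because the data are counts, a Poisson or negative binomial rate model is preferable, with period as the factor and patient as the cluster, reported as a rate ratio with 95% CI. For consistency, name a paired method such as McNemar's test for the number of patients admitted.

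The cost is wording in two places, with no new data. If it is handled as a protocol amendment, Methods/design requires ethics committee approval and an update to the trial registry.

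This change does not guarantee the stated 80% power. The 97 needs its own justification, with a stated baseline rate, a within-patient correlation and a clear statement of whether the 20% is relative or absolute; that is a separate matter.

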## Sample size

Sample sizes have been calculated for the quantitative measurements. For evaluating changes in health worker knowledge of COPD management, the scores from the objective knowledge test in *BE WELL Health Provider Impact Questionnaire* will be used. The sample size, based on pilot data demonstrating change in knowledge score of 7 marks [standard deviation (SD) 4.5] [32], requires eight AHW participants, with a power of 80%, alpha 0.05, allowing for a 20% dropout (i.e. two AHWs per ACCHS). For the patient outcomes, based on our pilot study in rural and remote areas, to detect a change in 6MWT of 48 m, SD 70 m [11], with a power of 80% and alpha 0.05, 40 patients will be required, allowing for a 15% dropout. For quality of life, to detect a minus 4-point improvement in SGRQ (which is the minimal important difference [33]) with SD 6 points, 42 patients will be required, allowing for a 15% dropout, with power 80% and alpha 0.05. For hospitalisations, we have conservatively assumed a 20% reduction in hospital admissions. Therefore 97 patients would be needed, power 80%, alpha 0.05, allowing for 15% drop-out. Based on the largest patient sample size required, 97 patients with COPD will be recruited. For qualitative data, focus groups and interviews will be undertaken with participants until no new information is obtained and saturation is achieved.

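### The 97-patient target claims 80% power for a 20% fall in admissions without a baseline, and the claim fails over a wide range of plausible baselines

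*Protocol article*

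**What the plan says.** The Sample size section of the protocol article gives separate calculations for health-worker knowledge, 6MWT, SGRQ and hospitalisations. The first three each state a difference and an SD. The hospitalisation calculation states only a percentage and draws the number from it: "For hospitalisations, we have conservatively assumed a 20% reduction in hospital admissions. Therefore 97 patients would be needed, power 80%, alpha 0.05", the sentence ending "allowing for 15% drop-out". That number then governs the study: "Based on the largest patient sample size required, 97 patients with COPD will be recruited".

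The Data and data analysis section plans two hospitalisation analyses. Respiratory admission counts "in the 12 months before and after the *BE WELL* PR program will be compared using unpaired t-tests". In addition, "the number of patients admitted before and after program will compared using proportions". The Sample size section does not say which of the two the figure 97 belongs to, or whether the 20% is relative or absolute.

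**The concern.** A percentage reduction alone does not determine a sample size. A count needs a baseline mean and a variance; a proportion needs two proportions and, in a before-after design, their correlation. None of these is given, so a reader cannot derive 97 from what is printed. The article nevertheless attaches a definite power to it and calls the effect size conservative.

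Hospitalisation and its cost form part of Objective 4, and savings from reduced health care use are to be quantified. If the stated power is taken at face value, a null hospitalisation result would be read as a well-powered negative. If patients average one or two admissions a year, the study would more often than not miss a true 20% reduction.

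**Working it through.** **Inputs from the article.** 20% reduction, 80% power, alpha 0.05, 15% dropout, 97 recruited. Evaluable patients: 82, since 82/0.85 = 96.5, rounded up to 97. Sidedness is not stated. I take two-sided, because the 6MWT figure reproduces that way: 2 × 7.849 × (70/48)² = 33.4, so 34, and 34/0.85 = 40 as stated. Here 7.849 = (1.96 + 0.8416)².

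**Assumptions not in the article.** Baseline rate μ of 0.5 to 4.3 admissions per patient-year, with Poisson variance.

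**Can 97 be reproduced?** Not from the stated inputs. It can be reproduced as two independent proportions 20 points apart, using the pooled formula for 40% versus 20%:

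(1.96 × √(2 × 0.3 × 0.7) + 0.8416 × √(0.24 + 0.16))² / 0.2² = 81.2, so 82, and 82/0.85 gives 97.

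By symmetry, 80% versus 60% gives the same result. In relative terms these are falls of 50% and 25%. (60% versus 40% also gives 97, but before any dropout allowance.) The 6MWT figure follows a two-group formula as well, which makes this origin plausible without proving it.

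**Reading 1: admission count, 20% relative fall.**

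- Two-sample formula: μ = 7.849 × 1.8 / (0.04 × 82) = 4.31 admissions per patient in the prior year.
- Paired, conditioning on total events: the after-share is 0.8/1.8 = 0.444, which is 0.0556 from one half. Events needed = (1.96 × 0.5 + 0.8416 × √(0.444 × 0.556))² / 0.0556² = 633, and 633/(82 × 1.8) = 4.29.

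Pairing therefore does not lower the threshold under Poisson variance, because each patient's year-to-year count variation remains. If all 97 were evaluable the threshold would be about 3.6 per year; with a one-sided test and 82 patients, about 3.4.

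Power by formula is Φ(0.2μ / √(1.8μ/82) − 1.96). I checked it by simulating paired t-tests (20,000 runs). The detectable relative fall x solves (2 − x)/x² = 82μ/7.849. Recruitment is 7.849 × 1.8/(0.04μ), rounded up, divided by 0.85 and rounded up.

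| Assumed admissions per patient-year | Power, formula | Power, simulated paired | Fall detectable with 80% power | Recruitment for 80% power at a 20% fall |
|---|---|---|---|---|
| 0.5 | 16% | 15% | 53% | 832 |
| 1 | 27% | 26% | 39% | 417 |
| 2 | 48% | 47% | 29% | 209 |
| 3 | 65% | 64% | 24% | 139 |
| 4.3 | 80% | 79% | 20% | 98 |

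**Reading 2: proportion admitted, 20% relative fall.** With the same pooled formula, 50% to 40% needs 388 and 60% to 48% needs 270 before dropout. The requirement comes down to 83 at a baseline of 88% and 78 at 89%, so 82 fits only if about 88% of patients were admitted in the prior year.

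**Reading 3: proportion admitted, 20-point absolute fall, paired.** McNemar sample size is (1.96√p_d + 0.8416√(p_d − 0.04))² / 0.04, where p_d is the proportion of discordant patients. For 40% to 20%:

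- Before and after independent: p_d = 0.32 + 0.12 = 0.44, giving 84.
- 80% of those admitted afterwards also admitted before: p_d = 0.24 + 0.04 = 0.28, giving 53.

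So 82 analysed is roughly enough, or more than enough, under this reading.

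**The case against.** The strongest reply is that the article plans a proportion-admitted analysis, that 97 reproduces under it as a 20-point drop, and that a paired calculation then needs only about 53 to 84 patients. This stands. A reader might infer from the count calculation that the design has 80% power only above four admissions a year. The article does not support that, because the count is one of two planned hospitalisation analyses and the sentence does not say which it serves. What the reply does not rescue is the wording: a drop from 40% to 20%, or from 80% to 60%, is neither a 20% reduction in admissions nor conservative.

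A reader might also infer an arithmetic slip. No stated inputs lead to a wrong output, so that is not shown either. The full protocol may give the baseline, and an article need not carry it. That excuses the missing baseline, but not a printed effect size and power that disagree with the calculation that most naturally yields 97.

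Hospitalisation is listed as a secondary outcome in the Abstract, and 97 exceeds the stated needs for 6MWT (40) and SGRQ (42). Nothing here suggests that those outcomes are short of patients.

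Finally, the planned unpaired t-test would lose further power if patients differ widely in admission rate. Simulated power near 9% at one to two admissions a year needs very strong variation (gamma dispersion of 1); at dispersion 0.5 it is about 15% to 21%. That is a fault of the test, separate from this point, and it is not counted in the figures above.

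**Conclusion.** The concern holds in this form: the stated 80% power for a 20% reduction is not supported by what is printed, and it fails over a wide range of baselines. On the count, it needs about 4.3 admissions per patient-year; at 0.5, 1 or 2 per year, power is about 15%, 27% or 47%. On the proportion admitted, a 20% relative fall needs a baseline near 88%. Only a 20-point absolute drop fits 97 comfortably, and that is a larger effect than the text describes.

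The conclusion rests on two-sided testing, 82 evaluable patients and, for the count, Poisson variance. Poisson is favourable compared with overdispersed counts but is not a strict bound, since underdispersion would lower the threshold. The baseline rates are assumptions shown as a range. The derivation of 97 is inferred.

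**What to change.** Keep 97 recruited and restate what it supports. Say which hospitalisation endpoint the figure refers to, its baseline value and source, and whether the 20% is relative or absolute.

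- If it is the proportion admitted with a 20-point drop, give the two proportions and support the number with a paired (McNemar) calculation, including the assumed overlap between the two years.
- If it is the admission count, replace the 80% power claim with the reduction that 82 patients can detect under a paired analysis, for example about 39% at one admission per year or 29% at two.

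In either case, remove the word conservatively and report the change in hospitalisations with a confidence interval.

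The cost is rewording one paragraph and accepting a less favourable statement of power or effect size. No extra patients are needed.
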